### 6.1 Inclusion criteria

Patients will be included in the eligible study population if

- they are aged at least 35 years and less than 80 years old, and
- as determined by their GP, they meet national age, sex and ethnicity guideline criteria for CVD risk assessment (Table 1) and repeat assessment recommendations (Table 2)

Table 1 Age to start cardiovascular disease and diabetes risk assessment

| Table 1 The age to start cardiovascular disease and diabetes risk assessment                                                                                                                                                                                                                                                                                                                                                                                                                                                                                                            |                                     |              |
|-----------------------------------------------------------------------------------------------------------------------------------------------------------------------------------------------------------------------------------------------------------------------------------------------------------------------------------------------------------------------------------------------------------------------------------------------------------------------------------------------------------------------------------------------------------------------------------------|-------------------------------------|--------------|
| Group                                                                                                                                                                                                                                                                                                                                                                                                                                                                                                                                                                                   | Men                                 | Women        |
| Asymptomatic people without known risk factors                                                                                                                                                                                                                                                                                                                                                                                                                                                                                                                                          | Age 45 years                        | Age 55 years |
| Māori, Pacific peoples or people from the Indian subcontinent*                                                                                                                                                                                                                                                                                                                                                                                                                                                                                                                          | Age 35 years                        | Age 45 years |
| People with other known cardiovascular risk factors or at high risk of developing diabetes                                                                                                                                                                                                                                                                                                                                                                                                                                                                                              | Age 35 years                        | Age 45 years |
| Family history risk factors                                                                                                                                                                                                                                                                                                                                                                                                                                                                                                                                                      |                                     |              |
| 

• Diabetes in first-degree relative (parent, brother or sister)

• Premature coronary heart disease or ischaemic stroke in a first-degree relative (father or brother <55 years, mother or sister <65 years)

                                                                                                                                                                                                                                                                                                               |                                     |              |
| Personal history risk factors                                                                                                                                                                                                                                                                                                                                                                                                                                                                                                                                                    |                                     |              |
| 

• People who smoke (or who have quit only in the last 12 months)

• Gestational diabetes, polycystic ovary syndrome

• Prior blood pressure (BP) <math>\geq 160/95</math> mm Hg, prior TC:HDL ratio <math>\geq 7</math>

• Known IGT (impaired glucose tolerance) or IFG (impaired fasting glucose)

• BMI <math>\geq 30</math> or truncal obesity (waist circumference <math>\geq 100</math> cm in men or <math>\geq 90</math> cm in women)

• eGFR† <math>< 60</math> ml/min/1.73 m^2

 |                                     |              |
| People with diabetes                                                                                                                                                                                                                                                                                                                                                                                                                                                                                                                                                                    | Annually from the time of diagnosis |              |

\* People from the Indian subcontinent = Indian, including Fijian Indian, Sri Lankan, Afghani, Bangladeshi, Nepalese, Pakistani, Tibetan.

† Estimated glomerular filtration rate (eGFR).

Table 2 Frequency of CVD and diabetes risk assessment

| Table 4 Frequency of cardiovascular risk assessment                       |                                     |
|---------------------------------------------------------------------------|-------------------------------------|
| 5-year risk $< 5\%$                                                       | Further risk assessment in 10 years |
| 5-year risk 5–10%                                                         | Further risk assessment in 5 years  |
| 5-year risk 10–15%                                                        | Further risk assessment in 2 years  |
| 5-year risk $\geq 15\%$ , diabetes, or on lipid or BP lowering medication | Annual risk assessment              |

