## 6. Study Design

This is a pragmatic, prospective, open, blinded endpoint, cluster randomised controlled non-inferiority trial in primary care.

The study setting is the patients enrolled in GP practices within the Northland region of New Zealand that belong to either Manaia Health Primary Healthcare Organization (PHO) or Te Tai Tokerau PHO. Manaia Health has 24 practices and Te Tai Tokerau has 15. A cluster randomised controlled trial is proposed within twenty of these general practices who use PREDICT and agree to participate in the study.

The eligible population is comprised of patients enrolled in these practices who are aged between 35-79 years, who as determined by their GP, meet age, sex and ethnicity guideline criteria for CVD risk assessment (Table1) and do not have a previous recorded CVD risk assessment or if they have had a previous CVD risk assessment are overdue for their next check (Table 2). All CVD risk assessment data will be automatically captured within the PREDICT server before, during, and after the study as part of usual clinical practice.

The unit of randomisation will be the practice and data collection will be at the individual patient level. The study involves random allocation of the practices to either the POC group (Cobas b 101) or laboratory (control) group. A cluster RCT design was necessary because the cobas b 101 device will be provided to the practice as a cluster level intervention.

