### 6.3 Recruitment

The PHOs will invite practices to join the study. Interested practices will be visited and twenty practices who agree to be part of the study will be randomised. The eligible population will be identified automatically and anonymously through an existing CVD population register held by the PHOs and PREDICT. Notices informing patients about the study will be placed in GP waiting rooms of practices who have been allocated to the POC group and an Information Sheet will be available (Appendix 2).

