## 6.12 Detail of data collection

### 6.12.1 Eligibility, randomisation and baseline assessment

All practices in Manaia and Te Tai Tokerau PHOs will be eligible to be included in the study. The first twenty to provide informed consent will be randomised. A de-identified list of eligible patients in the participating practices will be generated using the Northland PHOs' population register provided by PREDICT.

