### 6.12.2 CVD risk assessment data collection

CVD risk assessment data will be collected by the PREDICT software. At the end of the study the investigators will receive de-identified PREDICT data by practice on the study population who have had a completed or parked CVD risk assessment. The PREDICT data will be provided to the investigators by practice separated into two groups. At the end of the analysis the allocation assignment to POC or laboratory group will be revealed to the investigators.

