## 7. Statistical Considerations

### 7.1 Sample size

The study will involve a two-arm parallel cluster randomised controlled trial (CRCT) design with 20 practices (10 practices per arm). The primary outcome is whether the eligible patients have had a completed CVD risk assessment during the study. Preliminary analyses indicated that at least 70% of the enrolled populations within Manaia and Te Tai Tokerau PHOs have had a completed CVD risk assessment since 2006. Many of these people will be due for repeat CVD risk assessment. Significant delays to the conduct of this trial have occurred both prior to commencement and having to halt the trial due to manufacturing problems of the HbA1c discs. During this time practices have accelerated their CVD risk assessments in order to meet the national target (by July 2014 that 90% of the eligible population have had a CVD risk assessment in the previous 5 years.) As at April 2014, the two PHOs have screened approximately 80% of their eligible enrolled populations over the last five years. Therefore this trial now needs to adopt **a priori a non-inferiority hypothesis**.

Our previous sample size calculations May 2013, were as follows; We assumed a primary event rate of 70% in the laboratory group and a 10-15% increase to 85% in the POC group. This figure is based on a study set in community pharmacies where POC testing for cholesterol risk management led to a 10% increase. Taking into account an intraclass correlation coefficient of 0.025 as suggested by Elley et al (2005) from three New Zealand CRCTs; a 5% two-sided level of significant test and study power of 90%, we estimate a minimum sample size of 1000 risk assessments is needed (on average 50 patients per practice).

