### Key milestones

| Date           | Milestone                                                                                   |
|----------------|---------------------------------------------------------------------------------------------|
| May 2013       | Ethics submitted                                                                            |
| June 2013      | Ethics approval                                                                             |
| July 2013      | Recruit practices                                                                           |
| August 2013    | Start of study                                                                              |
| August 2013    | Study halted due to manufacturing problems cobas b 1010 discs                               |
| May 2014       | Study recommenced after re-validation cobas discs, retraining practices and Ethics approval |
| June 2015      | Estimated end of study                                                                      |
| September 2015 | Analysis complete.                                                                          |
| November 2015  | Paper submitted.                                                                            |

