| 4/5  | Study Management Committee Members | From: [name]
To: A/[name]
From: Assoc [name]
To: [name]
From: [name]
To: [name]
Updated Committee Member details
[name] new Project Manager replacing [name]                                                                                                                                                   |
| 7    | NIHI Signatory                     | From: [name]
To: A/[name]
From: Assoc [name]
To: [name]                                                                                                                                                                                                                                                                                                              |
| 7    | Revision Chronology                | Version 4 – 30 March 2015 – Amendment 3
New version information added                                                                                                                                                                                                                                                                                                                                                        |
| 10   | Investigators and study centres    | From: [name], [name], Assoc [name], The University of Auckland.
To: A/[name], [name], [name], The University of Auckland.                                                                                                                                                                                                                                          |
| 12   | Study Plan Schematic               | Added: End of study practice questionnaire to Laboratory group arm                                                                                                                                                                                                                                                                                                                                                              |

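### The primary denominator is defined in two incompatible ways: by the judgement of GPs who know their arm, and by an automatic Week 0 register list

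*Protocol*

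**What the plan says.** All references are to the protocol.

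- **GP rule.** Section 6 (Study Design) describes enrolled patients aged 35-79 "who as determined by their GP, meet age, sex and ethnicity guideline criteria for CVD risk assessment (Table1" and who are unassessed or overdue. Section 6.1 repeats it: "as determined by their GP, they meet national age, sex and ethnicity guideline criteria for CVD risk assessment (Table 1". Appendix 6 attributes the GP phrase to "Version 4 – 30 March 2015 – Amendment 3".
- **Register rule.** Section 6.3: "The eligible population will be identified automatically and anonymously through an existing CVD population register held by the PHOs and PREDICT". Section 6.12.1: "A de-identified list of eligible patients in the participating practices will be generated" from the PHOs' population register. The follow-up table in section 6.12.3 marks the eligible population under the Week 0 PREDICT column and the risk assessments under the end-of-study PREDICT column.
- **Outcome.** Section 7.1: "The primary outcome is whether the eligible patients have had a completed CVD risk assessment during the study". The non-inferiority margin is 5 percentage points.
- **End-of-study data.** Section 6.12.2: investigators receive PREDICT data "on the study population who have had a completed or parked CVD risk assessment".
- **Who knows what.** Section 6.6 says practices cannot be blinded. Section 8 leaves the choice of whom to assess with clinical staff.
- **Dates.** In the key milestones of Appendix 5, the entry for May 2014 reads "Study recommenced after re-validation cobas discs, retraining practices and Ethics approval". The estimated end of study is June 2015.

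**The concern.** Whoever decides which patients are eligible decides the denominator of the primary outcome. A register list drawn at Week 0 does not depend on what a practice does afterwards. A GP's judgement can depend on it, because the GP knows whether the practice has the device and sees which patients come in. Several triggers in Table 1 of section 6.1, such as family history and truncal obesity, need clinical ascertainment, so judgement can change who counts.

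If unassessed patients were judged ineligible more often in one arm, that arm's completion rate would rise without one more assessment being done. The comparison would then no longer be of the populations that were randomised. In a non-inferiority trial, a shift in favour of the POC arm can hide a real deficit.

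**Working it through.** **1. The two rules side by side**

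| | GP rule (6, 6.1) | Register rule (6.3, 6.12.1, follow-up table) |
|---|---|---|
| Who decides | GP in an unblinded practice | Automatic, from the register |
| When | Not stated | Week 0 |
| Origin | Wording dated 30 March 2015 | No change listed in Appendix 6 |
| Can depend on arm | Yes | No, if drawn by algorithm |

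The study restarted in May 2014, so a Week 0 list predates the GP wording. The two cannot be one definition, and no section ranks them.

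**2. The plan's own figure**

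Inputs (section 7.1): 30% laboratory, 40% POC, margin 5 points, one-sided 0.025, 90% power, ICC 0.025, 50 patients per practice.

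- Per arm before clustering: (0.30×0.70 + 0.40×0.60) × (1.960 + 1.282)² / (0.10 + 0.05)² = 210.1, rounded up to 211.
- Design effect: 1 + 49 × 0.025 = 2.225.
- 211 × 2.225 = 469.5, so 470 per arm and 940 in total. The stated figure reproduces.

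The formula counts eligible patients, of whom 30% or 40% complete. Section 7.1 nevertheless labels the 940 as risk assessments. At the planning rates, 470 per arm would give 141 + 188 = 329 completed assessments. The sample-size text therefore does not settle the denominator either.

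**3. Effect of leaving out unassessed POC patients (illustration)**

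Assumed, not in the protocol: a list of 1,000 POC patients, 250 completed (25%), and exclusions only among the 750 POC non-completers.

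- 10% judged ineligible: 75 removed, 250/925 = 27.0%, a rise of 2.0 points.
- 20% judged ineligible: 150 removed, 250/850 = 29.4%, a rise of 4.4 points.

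**4. Effect on the error rate (illustration)**

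Assume the true rates lie exactly at the margin, 25% POC against 30% laboratory, with 470 per arm. The effective size is 470/2.225 = 211.2 per arm. Let x be the share of the whole POC list left out, all of it unassessed. Then the apparent POC rate is a = 0.25/(1−x), SE² = a(1−a)/[211.2(1−x)] + 0.30×0.70/211.2, and the chance of declaring non-inferiority is Φ[(a − 0.30 + 0.05)/SE − 1.960].

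| x | Apparent POC rate | Chance of declaring non-inferiority |
|---|---|---|
| 0 | 25.0% | 2.5% |
| 5% | 26.3% | 4.8% |
| 7.5% (10% of non-completers) | 27.0% | 6.6% |
| 10% | 27.8% | 8.9% |
| 15% (20% of non-completers) | 29.4% | 15.7% |

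This is a normal approximation with the design effect held at 2.225. With a denominator set independently of arm, x = 0 and the rate stays at 2.5%.

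**The case against.** The strongest reply is that the protocol already contains a denominator that the arm cannot influence. The follow-up table separates the Week 0 eligible population from the end-of-study assessments. The objective and the outcome both refer to eligible patients, and the 30% planning rate is a share of the eligible population. On that reading the end-of-study extract supplies only the numerator, and patients never started are already on the list. This stands: the restriction in section 6.12.2 is a problem only if the extract, and not the Week 0 list, is used as the denominator.

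A reader might infer from section 6.12.2 that the analysis will use completed plus parked records, and that POC would then win almost by construction because its results arrive at the visit. The documents do not support that. They point to a separate list, section 3.3 says the proportion left incomplete is unknown, and section 6.7 allows laboratory tests in the POC arm.

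It is also fair that no section describes a GP reviewing the list, removing a patient or recording ineligibility, and none says when the GP decides. Choosing whom to assess affects the outcome and does not by itself redefine eligibility. That the GP judgement falls after randomisation is an inference from the amendment date and the routine-care setting.

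Detail of analysis sets may be left to the SAP. But here the protocol itself states the population, and states it in two ways; an SAP cannot follow both.

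**Conclusion.** The contradiction is in the current text and concerns the denominator of the primary outcome. Sections 6 and 6.1 make eligibility the judgement of GPs who know their arm; sections 6.3 and 6.12.1 and the follow-up table take it from the register at Week 0. The protocol does not say which governs.

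The bias is conditional on the GP rule being applied to the denominator. The rises of 2.0 and 4.4 points, and the false non-inferiority rates of 4.8% to 15.7% for x between 5% and 15%, rest on an assumed true POC rate of 25% and on assumed exclusions confined to POC non-completers. They show that modest selection could use up much of the 5-point margin; they do not estimate selection in this trial. A reader might conclude that the intention-to-treat analysis has failed or that eligibility was in fact filtered by arm. The text shows neither, only that it does not rule the second out.

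**What to change.** - State that the primary analysis set is the register list produced by applying the age, sex, ethnicity and prior-assessment rules by algorithm, without regard to arm or GP judgement, at a named date.
- State whether patients who fall due during follow-up are added and, if so, by the same date-based algorithm in both arms. This matters because Table 2 puts some groups on annual assessment and the 30% planning rate covers a 12-month period; a list frozen once would miss people who become due later.
- Link PREDICT records to the list by encrypted NHI, and count listed patients without a completed record as not completed.
- State in section 6.12.2 that the end-of-study extract supplies outcomes only.
- Take the GP phrase out of the primary population in sections 6 and 6.1, and use GP-determined eligibility only in a sensitivity analysis.

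The cost is protocol wording and one linkage to a list that section 6.12.1 already foresees. The downside is that patients eligible only through risk factors not coded on the register leave the primary set. Randomisation makes that loss similar in both arms in expectation, though with 20 practices some chance imbalance is possible.
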